## Abstract

**Background:**

Cancer patients experience various forms of psychological distress. Their distress, mainly in the form of depression and anxiety, leads to poor quality of life, increased medical spending due to frequent visits, and decrease in treatment adherence. It is estimated that 30–50% among them would require support from mental health professionals: in reality, much less actually receive such support partly due to a shortage of qualified professionals and also due to psychological barriers in seeking such help. The purpose of the present study is to develop the easily accessible and the most efficient and effective smartphone psychotherapy package to alleviate depression and anxiety in cancer patients.

**Methods:**

Based on the multiphase optimization strategy (MOST) framework, the SMartphone Intervention to LEssen depression/Anxiety and GAIN resilience project (SMILE-AGAIN project) is a parallel-group, multicenter, open, stratified block randomized, fully factorial trial with four experimental components: psychosocial education (PE), behavioral activation (BA), assertion training (AT), and problem-solving therapy (PS). The allocation sequences are maintained centrally. All participants receive PE and then are randomized to the presence/absence of the remaining three components. The primary outcome of this study is the Patient Health Questionnaire-9 (PHQ-9) total score, which will be administered as an electronic patient-reported outcome on the patients’ smartphones after 8 weeks. The protocol was approved by the Institutional Review Board of Nagoya City University on July 15, 2020 (ID: 46-20-0005). The randomized trial, which commenced in March 2021, is currently enrolling participants. The estimated end date for this study is March 2023.

**Discussion:**

The highly efficient experimental design will allow for the identification of the most effective components and the most efficient combinations among the four components of the smartphone psychotherapy package for cancer patients. Given that many cancer patients face significant psychological hurdles in seeing mental health professionals, easily accessible therapeutic interventions without hospital visits may offer benefits. If an effective combination of psychotherapy is determined in this study, it can be provided using smartphones to patients who cannot easily access hospitals or clinics.

**Trial registration:**

UMIN000041536, CTR. Registered on 1 November 2020 https://center6.umin.ac.jp/cgi-open-bin/ctr/ctr_view.cgi?recptno=R000047301.

**Supplementary Information:**

The online version contains supplementary material available at 10.1186/s13063-023-07307-y.

## Background

It is estimated that there were 19.3 million new cancer cases and 10 million cancer deaths [1] worldwide in 2020. Cancer patients experience various forms of psychological distress, with 30–50% of them recommended to receive support from mental health professionals [2]. In the surveillance of Japanese cancer patients’ day-to-day concerns, the most frequent concern was psychological distress (33%) [3]. Among the developed countries, Japan has an extremely high suicide rate, and cancer patients account for a major proportion of suicides in general hospitals [4]. Moreover, the suicide rate increases 24-fold within 1 year after cancer diagnosis [5]. In this context, it has been demonstrated that depression, rather than physical distress, contributes to suicide [6]. Depression and anxiety impact the quality of life [7] of cancer patients, increase medical spending, decrease treatment adherence [8], and elevate morbidity [9]. Therefore, depression and anxiety are found to impair many important outcomes in cancer care and are among the most frequent and greatest concerns for cancer patients and their families [10–12]. However, the evidence base for depression treatment focuses on a single cancer, particularly breast cancer. Considering the heterogeneity in cancer populations, research is required to investigate the efficacy of depression treatment among all the cancer population [13].

Although the number of cancer patients continues to increase, we have not been able to palliate psychological distress to a satisfactory extent. While cancer patients expect appropriate care and intervention for their depression and anxiety and the efficacy of pharmacotherapy and psychotherapy is well known, most patients do not receive appropriate treatment. The number of healthcare professionals who treat psychological distress is limited compared to the number of cancer patients. Patients have a significant psychological hurdle in seeing mental health professionals. Since cancer patients have many physical symptoms owing to their condition and treatment, healthcare professionals need to be aware of appropriate medications and their interactions with anticancer drugs, and a high degree of specialization is required during treatment. Among other hurdles, as most patients hope to receive psychological treatment rather than psychotropic drug therapy [14], easily accessible psychological interventions have become imperative.

The usability of smartphone-based cognitive behavioral therapy (CBT) for depression in general psychiatry settings was shown in a randomized controlled trial (RCT) [15]. However, this therapy includes multiple components, and its usability for cancer patients has not been demonstrated [16]. Considering that there are often communication barriers with important “others”, such as family and medical staff, and the use of assertion skills in clinical practice, we have added smartphone assertion training. For smartphone problem-solving therapy, our previous clinical trials with breast cancer survivors, without a control group, indicated preliminary usability [17]. We considered the above combination, estimating it to be the most appropriate by our clinical experience.

This study aims to establish a treatment method based on evidence and develop the most appropriate psychological intervention to alleviate the symptoms of depression and anxiety experienced by cancer patients. In relation to the component of psychotherapy based on these forms of CBT, we will conduct a fully factorial RCT for cancer patients to estimate the effect of each component and develop the most efficient and effective smartphone psychotherapy package to address their depression and anxiety.

This protocol is in accordance with the Standard Protocol Items: Recommendations for Interventional Trials guideline [18]. The present study is subject to the ethical guidelines for clinical studies published by the Japanese Ministry of Education, Science and Technology and the Ministry of Health, Labor and Welfare, and the modified Act on the Protection of Personal Information, as well as the ethical principles established for research with humans stipulated in the Declaration of Helsinki and further amendments thereto. The report is based on protocol version 1.1, approved on July 15, 2020, by the Nagoya City University Graduate School of Medical Sciences and the Nagoya City University Hospital Ethics Committee.

## Methods/design

### The aim

The aim of this study is to develop the most efficient and effective smartphone psychotherapy package to address depression and anxiety in cancer patients after diagnosis to improve their quality of life.

### Design

The multiphase optimization strategy (MOST) is an innovative approach based on engineering and behavioral sciences that provides a principled and comprehensive framework for selecting intervention components among multicomponent interventions [19, 20]. It consists of three stages: (1) preparation to conduct an optimization trial; (2) optimization to reveal what constitutes an optimized intervention; and (3) evaluation of the optimized intervention for an established intervention in an RCT. This study represents the optimization phase, in accordance with the MOST framework, and uses a fully factorial design to allow for the estimation of the main effects of individual components and their interaction effects.

This study is a parallel-group, multicenter, open, stratified block randomized, fully factorial trial with four experimental components: psychoeducation (PE), behavioral activation (BA), assertion training (AT), and problem-solving (PS). PE is provided to everyone but the three other components will be coded at two levels (presence and absence).

In this design, the effect of a component is estimated by comparing the mean of all combinations, including that component, against the mean of all other combinations that do not include the component. Since both the former and the latter sets of combinations have equal credibility and nonspecific supportive elements, this design allows for the estimation of effects specific to that component and can uniquely overcome the issue of specificity in psychotherapy research [21].

### Participants

#### Setting of the study

This trial will take place at Nagoya City University Hospital, Tohoku University Hospital, the National Cancer Center Hospital, the National Cancer Center Hospital East and Shizuoka Cancer Center in Japan. Collaborating hospitals/clinics will be recruited in a later stage of the study.

#### Eligibility criteria for study centers

Collaborating hospitals/clinics will be recruited from core facilities in areas with many cancer patients in Japan, taking into consideration their willingness to participate.

#### Eligibility criteria for participants

Each participant must satisfy all of the following inclusion criteria and none of the exclusion criteria.

Inclusion criteria are as follows:1. Patients with a cancer diagnosis and awareness of the same diagnosis2. Patients aged 20 years or older3. Smartphone users who are capable of using an electronic patient-reported outcome (e-PRO) system with a smartphone4. Patients with an estimated prognosis of more than 6 months5. Patients who expect to concentrate on the intervention for about two months after participation in this study (e.g., those who do not plan to use cell-damaging anticancer drugs with strong side effects).

Exclusion criteria are as follows:1. Patients who do not understand Japanese2. Patients with psychiatric symptoms (e.g., dementia, cognitive impairment, and severe depression with suicide ideation) who have been identified by attending physicians as inappropriate for the study3. Individuals who have received face-to-face CBT4. Persons who received smartphone CBT or participated in our previous study, the “SMILE PROJECT.”

Eligibility criteria for study personnel are as follows:

Encouragement emails will be handled by personnel who are qualified in health care, such as nurses.

### Interventions

Figure 1 shows screenshots of the smartphone application. The components of smartphone psychotherapy are as follows:

**Fig. 1 Fig1:**
[figure not shown]
Smartphone psychotherapy. PE, psychoeducation; BA, behavioural activation; AT, assertion training; PS, structured problem solving

PE consists of materials regarding psychological stress, emphasizing the importance of self-checks of one’s own emotional state. This is a basic matter and will be provided to all the participants.

BA includes PE on the importance of pleasurable activities according to the principle “When your body moves, so does your mind.” It includes a worksheet for a personal experiment to test a new activity and a gamified “action marathon” to promote such personal experiments.AT consists of PE on assertive communication, in contrast to aggressive or passive communication. The participants will learn how to express their emotions and desires without hurting others or sacrificing their own pleasures.Structured problem solving (PS) teaches the participants how to evaluate the issues at hand, specify a concrete and achievable objective for the issue, conceptualize possible solutions, compare their advantages and disadvantages, and finally choose the most desirable action and perform it. A worksheet will be provided to guide the participants through this process.

Each component consists of a lesson that is supposed to take 1 week to complete. The participants can move to the next lesson only after 1 week has passed and after they have completed one worksheet.

PE constitutes the core element of the intervention, and all participants will receive this component. After completing PE, the participants will be randomly allocated to one of the combinations on the basis of the presence/absence of the remaining three components (Fig. 2).

**Fig. 2 Fig2:**
[figure not shown]
Flow, enrollment, intervention, and assessment schedule

To enable examination of the ordering effects between BA and PS, we doubled the number of combinations to 2^3^ × 2=16.

#### Strategies to improve adherence to interventions and procedures for monitoring adherence

The participants will receive a semiautomated email acknowledging their progress every week. The message is based on a template that focuses on adherence and motivation but can be modified by nurses on the study team. It can include technical advice for the program, but no therapeutic content with regard to CBT is allowed.

The participants’ adherence to the allocated intervention will be recorded and uploaded by the online server system. The study personnel will have access to the server and perform ongoing monitoring of the participants’ adherence.

#### Concomitant treatment

There is no restriction on concomitant treatments, except for specialized CBT.

#### Termination rules for participants

Discontinuation of protocol treatment

If a participant meets any of the following conditions, the research team can discontinue their access to the application. However, the participant will not be considered to have dropped out of the trial at that stage and will receive the protocol assessments if (1) the participant intends to stop the protocol treatment; (2) the research team judges that the risk of the protocol treatment is greater than the benefit for any reason; (3) the research team evaluates that it is difficult to continue the protocol treatment owing to clinical deterioration; and (4) the research team assesses that it is inappropriate to continue the protocol treatment for any reason (e.g., when identity theft, duplicate entry, etc., are detected).

## Anticipated risks and benefits for the participants

The intervention will consist of various amounts of PE and exercises in cognitive and behavioral skills for stress reduction conducted as self-help programs by the participants on their smartphone. The interventions will therefore be considered as “interventions with minimal invasiveness,” and no serious health risks are expected, except for possible psychological and time burdens while going through the program and responding to the questionnaires.

The possible psychological and time burdens will be fully disclosed and explained to the potential participants in video instructions and on the homepage, and only those who have provided e-consent will be recruited for this study. No insurance scheme is therefore planned.

However, the possibility of serious adverse events (SAEs), whether related to study participation or not, cannot be negated, as would normally be expected of the participants in their lives. All participants will be closely monitored, and they will be provided standard care in their hospitals. Any expenses necessary for such services will be handled as usual. On the other hand, participants can expect to learn about psychological stress and how to maintain mental health through the program. However, the extent of such benefits is the theme of this trial and is currently unknown.

## Description of materials

### Measurements

Table 1 shows the schedule for the outcome measurements.

**Table 1 Tab1:**
[figure not shown]
Schedule for the outcome measurements

### Primary outcome measure

The primary outcome is the self-administered Patient Health Questionnaire-9 (PHQ-9) [22] score at week 8.

### Secondary outcome measure

The secondary outcome is the self-administered Generalized Anxiety Disorder-7 (GAD-7) [23] score at week 8.

### Background characteristics

The following background characteristics will be measured at baseline.1. DemographicsaAgebSexcMarital status (married/partnered, divorced/separated/bereaved, single)dEducation (6, 9, 12, 14, 16, >16 years)eEmployment status (full-time, part-time, home duties, unemployed)fTime since cancer diagnosis (>1 year, 1–3 years, 5–10 years, >10 years)gOriginal cancer site (breast, lung, stomach, colorectal, liver, uterus, ovary, prostate, head and neck, malignant lymphoma, other).hCancer stage (0, I, II, III, IV, unknown, other) at cancer diagnosisiCurrent cancer stage (0, I, II, III, IV, unknown, other)jPrevious cancer (Y/N)kCancer treatmentiSurgery (Y/N)iiRadiation therapy (Y (past, current)/N)iiiHormone therapy (Y (past, current)/N)ivChemotherapy (Y (past, current)/N)vTargeted therapy (Y (past, current)/N)viImmunotherapy (Y (past, current)/N)l. Eastern Cooperative Oncology Group Performance status (ECOG PS) (0, 1, 2)m. Hospital (Nagoya City University Hospital, Aichi Cancer Center, Tohoku University Hospital, the National Cancer Center Hospital, the National Cancer Center Hospital East, Shizuoka Cancer Center)n. Experience of consulting a doctor of psychiatry or psychosomatic medicine (past) (Y/N)o. Experience of consulting a doctor of psychiatry or psychosomatic medicine (current) (Y/N)p. Having tranquilizer or hypnotic drugs (Y/N)2. PersonalityaShort form of the Big Five scale (29 items) [24]3. Social supportaSocial Support Questionnaire (12 items) [25]4. Cognitive and behavioral skillsaSelf-monitoring (five items) [26]bCognitive restriction (six items) [27]cBehavioral activation: Behavioral Activation for Depression Scale-Short Form (eight items) [28]dAssertiveness (seven items) [29]eProblem solving (six items) [30]5. Clinical characteristicsaPHQ-9 [22] scoresbGAD-7 [23] scores

### Patient health questionnaire-9 (PHQ-9) [22]

The PHQ-9 consists of nine diagnostic criteria items for an MDE in the *Diagnostic and Statistical Manual of Mental Disorders, Fourth Edition* (DSM-IV) [31] and the DSM-5 [32]. Each item is rated from 0 (*Not at all*) to 3 (*nearly every day*), with a total score ranging between 0 and 27. The reliability and validity of the original PHQ-9 and its Japanese version are well established [33, 34]. We changed the PHQ-9 recall time frame from 2 weeks to 1 week to measure weekly depression severity in this study [35].

## Generalized anxiety disorder-7 (GAD-7) [23]

The GAD-7 questionnaire was developed to measure the severity of generalized anxiety and includes seven items representing nervousness, tension, and worry. Each item is rated from 0 (*not at all*) to 3 (*nearly every day*), with the total score ranging between 0 and 21. Its reliability and validity have been established [23]. We changed the GAD-7 recall time frame from 2 weeks to 1 week to measure anxiety severity in this study [35].

## Big five scale of personality trait adjectives [36]

We will use the short form of the Big Five Scale of Personality Trait Adjectives, which is commonly used in Japan. The reliability and validity of the short version have been ascertained [24]. Each of the five personality traits of neuroticism, extraversion, openness, agreeableness, and conscientiousness will be measured with five to seven corresponding adjectives on a 5-point Likert scale from 0 (*Untrue of me)* and 4 (*True of me)*. We excluded the option “neither”, which is used in the original version [35].

## Social support questionnaire [25]

We will measure the size and quality of a patient’s social support using the short form of the Social Support Questionnaire. It measures the number of persons providing support and the satisfaction with such support in six domains. The reliability and validity of the original scale [25] and its Japanese version [37] have been satisfactory.

## Cognitive and behavioral skills

To measure each of the cognitive or behavioral skills for the three components in this trial, we will use the Short Cognitive Behavior Therapy Skills scale, whose reliability and validity have been established [38]. It measures a patient’s skills in BA, PS, and AT.

With regard to BA, we used the BA subscale of the Japanese Behavioral Activation for Depression Scale-Short Form [39], translated from the original English version [28], and validated it in the Japanese population. The Japanese version consists of five items, each rated from 0 (*very untrue) to* 3 (*very true).*

For AT, we will use the self-assertion subscale of the Adult Social Skills Scale, developed and validated by Aikawa et al. [29]. It comprises seven items, each rated between 0 *(very untrue of me)* and 3 *(very true of me).* Its reliability and validity have been established [29].

For PS, we will select the six highest loading items of the approach-avoidance style subscale of the Problem-Solving Inventory [30]. The reliability and validity of the original version have been established, and those of the Japanese version have been shown in another study. Each item is rated from 0 *(very untrue of me)* to 3 *(very true of me)*, and the total score ranges between 9 and 18.

### Procedure

#### Participant flow

Figure 1 shows the participant flow, enrollment, intervention, and assessment schedule.

#### Recruitment

Oncologists in the core cancer hospitals will introduce this research to subjects by giving them a card containing a QR code linked to the research homepage. Those who are interested in participating in the research will apply for participation from the homepage, and an email requesting participation will be sent to the secretariat. We will start sampling at Nagoya City University Hospital and then extend recruitment to the other core cancer hospitals in Japan. In the second year of the study, we will seek collaboration from several other core cancer hospitals/clinics in Japan.

#### Research managing system

This is a fully decentralized individually randomized, parallel-group multicenter trial that the subjects could participate into the trial without involving in-person contact which is similar to our previous study [40] (Fig. 3). The study’s website (http://smileagain-project.org/) provides further information.

**Fig. 3 Fig3:**
[figure not shown]
Study management system

The website explains the purpose of the study and the eligibility criteria and methods used; it also features a video that briefly introduces the study as well as provides full written information about it. The clinical research coordinators (CRCs) at the central office will ascertain their eligibility by telephone.

#### Electronic informed consent and randomization at week 0

After screening, the CRCs will seek to obtain the subjects’ electronic informed consent (e-consent) via the e-PRO system at week 0. Participants will be asked to upload a picture of their identification materials (patients will be especially encouraged to attach a photo of the ID card from the hospital where they made regular follow-up visits for cancer). This e-consent procedure is in accordance with the guidance of the US Food and Drug Administration. The original informed consent material is shown in the online Supplementary appendix.

After providing e-consent, completing the baseline investigation by the e-PRO system and and completing the PE component, the participants will be randomly allocated to one of the combinations using the electronic data capturing (EDC) web program at the data management center (Fig. 3). The random allocation will therefore be concealed.

If participants are allocated to the intervention group, which does not include all three components, they will be informed that the use of the remaining components can be resumed, if they wish, after week 24.

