#### Assignment of interventions

Randomization and allocation concealment

The allocation will be stratified by the baseline PHQ-9 score (9 or less vs. 10 or more). We will use permuted block randomization to ensure balance in the number of subjects allocated to each combination because in the fully factorial design, imbalance in the allocated numbers among the factors would reduce the statistical power of the study. An independent data center will generate computer-generated random allocation sequences, which are maintained centrally, and the results of the assignment will determine which components are presented to the participants on their smartphone.

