## Blinding

Neither the participants nor the study personnel will be blinded to the intervention that each participant is receiving through the conduct of the trial. The assessment of all the primary and secondary outcomes will be self-reported by the participants and therefore not blinded. The statisticians will be blinded to the allocation through the statistical analyses by analyzing the datasets prepared by the study personnel in which all components are denoted only by a letter.

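### The notice about later access goes only to participants who lack a component, so the two sets compared for each main effect are given different information

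*Protocol article*

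**What the plan says.** The Protocol article, in the section Electronic informed consent and randomization at week 0, sets a condition, "If participants are allocated to the intervention group, which does not include all three components", and then an action: "they will be informed that the use of the remaining components can be resumed, if they wish, after week 24". The text stands directly after the description of random allocation and before the section on weeks 0-8, but gives no exact time for the notice.

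Three other places bear on it.

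- The Design section estimates a component's effect by "comparing the mean of all combinations, including that component, against the mean of all other combinations that do not include the component". It defends this contrast on the ground that "both the former and the latter sets of combinations have equal credibility and nonspecific supportive elements".
- The Blinding section states that "Neither the participants nor the study personnel will be blinded to the intervention that each participant is receiving", and that "The assessment of all the primary and secondary outcomes will be self-reported by the participants and therefore not blinded".
- The primary outcome is the PHQ-9 at week 8, so it is measured before the remaining components open.

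**The concern.** The notice depends on allocation. Participants with the full package have nothing outstanding and are not covered by it; everyone else is. Being told that parts of a programme will open later is a nonspecific element in the Design section's sense, and the protocol makes it unequal between the sets that each main effect compares. No reason for the difference is given.

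With open allocation and self-rated mood, a reaction to the notice could reach the PHQ-9 directly, and the analysis would credit it to the components. The shift would have the same sign for BA, AT and PS. At stake is the choice of components for the optimized package, which the plan makes at an unadjusted two-sided 5% level.

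**Working it through.** **Inputs.** From the Protocol article: eight presence/absence combinations, expanded to 16 cells ("we doubled the number of combinations to 2^3^ × 2=16"); equal cell sizes as the aim ("We will use permuted block randomization to ensure balance in the number of subjects allocated to each combination"); target effect 0.3 SD, two-sided alpha 0.05, power 0.80, total 350, raised to 16 x 22 = 352; possible extension to 787. Assumed: the effect of the notice on week-8 PHQ-9, called d, in SD units, positive when the notice worsens the score. The document gives no value for d, so a range is used that includes zero and both signs.

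**The plan's own figure.** Per level, n = 2 x (1.960 + 0.842)^2 / 0.3^2 = 174.4, so 175, or 350 in total. This agrees with the plan. At 352 the power is 0.804. For 0.2 SD the same formula gives 786, against the stated 787.

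**Who is notified.** Take BA; AT and PS follow by symmetry.

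- BA present: BA, BA+AT, BA+PS and BA+AT+PS. The first three are notified: 3/4 (6/8 in the 16-cell layout).
- BA absent: none, AT, PS and AT+PS. All are notified: 4/4 (8/8).

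Overall 7 of 8 combinations, or 14 of 16 cells, are notified.

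**Shift in a main effect.** Count benefit as positive (mean PHQ-9 without the component minus mean with it). The notice then adds d x (1.00 - 0.75) = 0.25d to each main effect. A least-squares fit of the notified indicator on the three component indicators over the balanced design gives a coefficient of -0.25 for each component, which is the same result.

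**Scale.** The standard error of a main effect at 352, in SD units, is sqrt(1/176 + 1/176) = 0.107; at 787 it is 2/sqrt(787) = 0.071. These ignore dropout and covariate adjustment. For a component with no true effect, the two-sided rejection rate is Phi(b/SE - 1.96) + Phi(-b/SE - 1.96), with b = 0.25d.

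| Assumed d (SD) | Shift b (SD) | b as share of 0.3 | Rejection rate, N = 352 | Rejection rate, N = 787 |
|---|---|---|---|---|
| -0.2 | -0.05 | -17% | 7.6% | 10.8% |
| 0 | 0 | 0% | 5.0% | 5.0% |
| +0.1 | +0.025 | 8% | 5.6% | 6.4% |
| +0.2 | +0.05 | 17% | 7.6% | 10.8% |
| +0.3 | +0.075 | 25% | 10.8% | 18.3% |

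In the first row most rejections would go against the component. The shift does not shrink as the sample grows, which is why the rates are higher at 787.

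**With the same notice in every arm**, exposure differs by 0 instead of 0.25, and the shift from this source is 0 whatever d is.

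**The case against.** The strongest reply is that d is the effect of the notice over and above what participants already know. They are unblinded, and their assigned components appear on their own phones. Someone who is given nothing after psychoeducation sees that without being told. The website offers full written information, and the consent material, in a supplement not shown here, may tell everyone about later access before allocation. The increment from one sentence could then be close to zero. A value of 0.3 SD would equal what the protocol expects from a whole therapy component, so the upper end of the range is hard to believe. All of this stands, and it keeps the point small.

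A reader might infer that the notice biases every main effect upward. The document does not support that. It says nothing about how participants respond, and an assurance of later access may be neutral or may soften disappointment, which would remove or reverse the shift.

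A reader might also infer that participants are told, at the moment of allocation, that treatment is being withheld from them. The text gives no exact time and is framed as use that becomes possible later if wished. It also does not say that full-package participants are otherwise kept unaware.

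A third tempting inference is that the full package will look better than the sum of its parts, since it alone is outside the notice. A notice effect would indeed load on interactions as well. But the primary model has no component-by-component terms, these interactions belong to the secondary analysis, and the argument again needs a harmful notice.

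What the reply does not remove is the unequal step itself. Even if everyone learns of later access beforehand, the individual notice is still directed at some allocations and not at one.

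**Conclusion.** The protocol prescribes a notice that reaches 100% of each component's absent set and 75% of its present set. This conflicts with the Design section's premise that the compared sets are alike in nonspecific elements. Any effect of the notice on PHQ-9 ratings would shift each main effect by a quarter of that effect: -0.05 to +0.075 SD for an assumed -0.2 to +0.3 SD, or at most about 0.7 of a standard error at 352 participants (0.075/0.107).

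The fractions follow from the document, given equal cell sizes. The size and direction of the notice effect are assumptions, and the quarter assumes that only being notified matters, not how many components are outstanding. Bias is therefore possible but not shown, and it is probably small. Severity is minor: a cheap improvement to the design, not an error that undermines it.

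**What to change.** Give every participant in all arms the same neutral information in the same words, before or at allocation: each person is assigned a version of the programme, and the whole programme is open to everyone after the week-24 assessment. Send the individual offer of remaining components only once the week-24 e-PRO is complete or its window has closed.

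Apply this to participants not yet allocated and record the date of the change. For those already notified, report the unequal notice as a limitation and qualify the Design section's statement about equal credibility.

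The cost is rewording one text and retiming one message, plus whatever the Protocol amendments section requires. Nobody loses access. The remaining weakness is that participants can still work out from the app or website what they lack, so the change reduces any bias without removing it.
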